Until just a few years ago, conducting research of this type, involving daily HRV measurements on each athlete and then adapting training based on these data, was only possible with the collaboration of high-cost laboratories. This study tests the use of noninvasive, commercial, low-cost and publicly accessible technology to evaluate the physiological responses obtained by adapting training to HRV.

Based on everything described above, we hypothesize that HRV-guided training will: (i) improve functional performance in high-level athletes and (ii) produce better performance results than a traditional training method. The objectives of the proposed protocol are: (i) to determine changes in the performance of high-level athletes after following an HRV-guided or a traditional training period, and (ii) to determine differences in the athletes’ performance after following both training protocols.

This will be a 12-week cluster-randomized controlled trial protocol in which professional athletes are assigned to either an HRV-based training group (HRV-G) or a traditional-based training group (TRAD-G). A block randomization method will be chosen to randomly assign participants to interventions in equally sized sample groups. This protocol has been designed following the Standard Protocol Items: Recommendations for Interventional Trials (SPIRIT) Statement [32]. To describe the intervention, the TIDieR (Template for Intervention Description and Replication) checklist by Hoffmann et al. [33] has been used.

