### 2.4. Outcomes

The primary outcome of this study will be the maximal oxygen uptake (VO_2max_) obtained in an incremental treadmill test. The secondary outcomes will be: the maximal speed in m/s, maximal heart rate, respiratory exchange ratio, ventilatory thresholds (VT1 and VT2) and their derived speed, heart rate, respiratory exchange ratio and VO_2_ obtained in the incremental treadmill test. Other measurements considered as secondary outcomes will be: the time, speed, heart rate, rating of perceived exertion (RPE) and lactate in the 3000 m running test. Body composition and rMSSD will be considered as other variables.

Measurements will be taken before and after the training period, which will correspond to weeks 5 (pretest) and 12 (post-test). Over the assessment weeks, care will be taken that participants do not carry out any high-intensity training sessions. Each assessment week will consist of two testing sessions with a 48-h recovery period. The first testing session will include maximal graded exercise test and body composition measurements. In the second testing session, athletes will perform a 3000 m running test. The rMSSD will be measured daily, as explained in the intervention section.

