### 2.8. Data Analysis

Data will be analyzed using Jamovi (Jamovi Project 2018, version 0.9.1.7, Sydney, Australia) and RStudio 3.15.0 software (PBC, Boston, MA, USA). Prior to data analysis, the Shapiro Wilk test and the Levene test will be performed to determine the normal distribution of the variables and the homogeneity of variance. Descriptive data will be reported as mean ± SD and range. All the data will be analyzed based on the intention-to-treat principle (last observation carried forward). If the sample is normally distributed, Student’s t-test will be calculated to compare variables before and after the intervention. For a variable to be considered as having a normal distribution, 95% of values will have to be within two standard deviations of the mean. If the sample is nonparametric, the U-Mann Whitney test will be used to compare variables before and after the intervention. The standardized mean differences (Cohen’s effect size) will be calculated together with the 95% confidence intervals [49]. The effect sizes (ES) will be calculated using Cohen’s d [49]. The relationship between variables will be assessed using the Pearson r correlation coefficient. If r is higher than 0.7, the determination coefficient (r^2^) will be used to determine the percentage of Y variation with regard to the X variation. Significance will be accepted at *p* ≤ 0.05.

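### Section 2.8 ties both outcome tests to a before-and-after comparison and names no HRV-G versus TRAD-G contrast, although hypothesis and objective (ii) are between groups

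*Protocol article*

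**What the plan says.** The Introduction sets two hypotheses side by side. The second is that HRV-guided training will "produce better performance results than a traditional training method". Objective (ii) matches it: "to determine differences in the athletes’ performance after following both training protocols". Objective (i) concerns change after either training period. The Discussion expects both groups to improve and HRV-G to do better.

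Section 2.4 makes VO2max the primary outcome and has the same athletes tested twice: "Measurements will be taken before and after the training period", in weeks 5 and 12.

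Section 2.8 gives the tests: "If the sample is normally distributed, Student’s t-test will be calculated to compare variables before and after the intervention", and otherwise "If the sample is nonparametric, the U-Mann Whitney test will be used to compare variables before and after the intervention". It does not say whether the t-test is paired. It also plans Shapiro-Wilk and Levene tests, Cohen's d with a 95% confidence interval (contrast not named) and Pearson correlations. It names no between-group test, change-score comparison, group-by-time term or baseline-adjusted model.

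Besides Shapiro-Wilk, it gives a second rule for calling a variable normal: "95% of values will have to be within two standard deviations of the mean".

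**The concern.** The comparison that is written down does not match the hypothesis that needs a control arm. If it is followed literally, each arm gets a before-after p-value, and a claim of superiority could rest only on one arm being significant and the other not. That is not evidence of a difference, least of all when both arms are expected to improve.

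The rank-based fallback adds a second problem. Mann-Whitney assumes independent samples, but the before and after values come from the same athletes. Ignoring the pairing makes the test very conservative when the two values are positively correlated. With 7 athletes per group there is little information to spare.

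The article does more than leave detail to an analysis plan: it names the tests and the comparison they are for.

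**Working it through.** **Inputs.** From section 2.5: 7 per group, SD 1.5 mL/kg/min, an estimated error of 1.1, and significance at 0.05 (taken as two-sided). The document gives no pre-post correlation ρ, so 0.5 to 0.9 is an assumed range. I take 1.5 as the SD of a single measurement and use 1.1/1.5 = 0.73 SD as an illustrative gain. Data are simulated as normal.

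**The plan's own power figure.** Section 2.5 states 93% power with 7 per group. A two-group F test with 1 and 12 degrees of freedom and a between-to-within variance ratio of 2 has noncentrality 7 × 2 = 14 and power 92.9%. This reproduces the figure. The power statement therefore fits a comparison of the two groups, which section 2.8 does not name.

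**Reading A: before against after within each arm.**

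*Mann-Whitney on 7 pairs.* The exact two-sided 5% region is U ≤ 8 or U ≥ 41. The signed-rank region is W ≤ 2 or W ≥ 26. The mean change is set at 1.3 SD of change, where the SD of change is √(2(1−ρ)) in units of the single-measurement SD.

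| ρ (assumed) | Mann-Whitney power | Signed-rank power | Mann-Whitney type I error |
|---|---|---|---|
| 0.5 | 55% | 78% | 0.9% |
| 0.7 | 31% | 78% | 0.3% |
| 0.8 | 17% | 78% | 0.1% |
| 0.9 | about 5% | 78% | below 0.1% |

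The signed-rank type I error is 4.5% to 4.8% throughout. Repeated simulations agree to about one percentage point.

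*Separate paired t-tests when both arms truly gain 0.73 SD.* The within-arm power p comes from the noncentral t with 6 degrees of freedom and noncentrality 0.73√7/√(2(1−ρ)). The chance that exactly one arm is significant is 2p(1−p).

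| ρ (assumed) | p | 2p(1−p) |
|---|---|---|
| 0.5 | 0.37 | 47% |
| 0.7 | 0.56 | 49% |
| 0.8 | 0.73 | 40% |
| 0.9 | 0.95 | 10% |

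The maximum is 50%, reached at p = 0.5. At a change of 1.3 SD of change, p = 0.82 and the chance is 2 × 0.82 × 0.18 = 30%.

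**Reading B: groups compared at each time point.** Mann-Whitney is then valid, but objective (i) has no test and the baseline is unused. The variance of the group difference relative to a post-only comparison is (1−ρ²) × (1 + 1/10) for ANCOVA with 7 per arm, where the second factor is the price of estimating the slope. For change scores it is 2(1−ρ).

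| ρ (assumed) | ANCOVA | Change score |
|---|---|---|
| 0.5 | 0.75 × 1.1 = 0.83 | 1.00 |
| 0.7 | 0.51 × 1.1 = 0.56 | 0.60 |
| 0.8 | 0.36 × 1.1 = 0.40 | 0.40 |
| 0.9 | 0.19 × 1.1 = 0.21 | 0.20 |

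**The 2-SD rule.** One value outside is 1/7 = 14% or 1/14 = 7% of the sample, so a single such value fails the rule. In 200,000 truly normal samples it fails 6% of samples of 7 and 42% of samples of 14.

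**The case against.** The best defence is that a between-group analysis was meant. Levene's test and Mann-Whitney both belong to independent groups, the power figure fits a two-group comparison, and Cohen's d with its interval could be the between-group estimate. This stands as a possible reading. A reader might infer that the plan contains no between-group estimate at all, and the text does not support that. It supports only that the contrast is not stated and that the stated comparison is a different one. Reading B also removes the paired-data complaint, but it leaves objective (i) untested and the baseline unused.

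Three further limits stand:

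- A reader might call both tests unsuitable. The t-test is suitable for objective (i) if paired, and the text does not say it is unpaired. Only Mann-Whitney, and only on Reading A, is clearly wrong.
- A reader might call hypothesis (ii) the main one. The Introduction does not rank the two.
- The loss from Mann-Whitney depends on a correlation that the document does not give. It is moderate at 0.5 and severe only at high correlation. The 42% failure rate likewise needs 14 pooled values. On Reading A the samples are of 7 and the rate is 6%.

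A comparison of change scores would also answer hypothesis (ii), and at correlations of 0.8 to 0.9 it is as precise as ANCOVA. The error is the missing contrast, not the absence of one particular model.

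**Conclusion.** The point holds in this form. Section 2.8 attaches its only two outcome tests to a before-and-after comparison and names no HRV-G versus TRAD-G contrast, while hypothesis and objective (ii) require one. Neither reading serves both objectives properly.

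If the within-arm reading is followed, two equally effective programmes would look different, by significance in one arm only, in about 10% to 49% of trials over assumed correlations of 0.9 to 0.5. The fallback test would run at a true error rate of 1% or less, with power of about 5% to 55% where signed-rank has 78%. If the other reading is followed, the cost is precision: baseline adjustment would cut the variance to between 0.83 and 0.21 of that of a post-only comparison. These sizes rest on the assumed correlations, normal data and the use of 1.5 as a single-measurement SD.

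The two unreconciled normality rules are a lesser point.

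A reader might also infer that better wording makes hypothesis (ii) fully answerable. The document does not support that. Section 2.1 names two clubs, and section 2.6 speaks of a club being randomised to HRV-G, while section 2.7 speaks of allocating participants. If whole clubs are allocated, any group difference is also a club difference.

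**What to change.** - **Primary analysis, objective (ii):** ANCOVA of post-test VO2max on group, adjusted for week-5 VO2max, reporting the adjusted HRV-G minus TRAD-G difference with 95% confidence interval and p-value. Use the same model for continuous secondary outcomes.
- **Objective (i):** report within-arm change with paired confidence intervals (paired t, or Wilcoxon signed-rank if ranks are wanted).
- **Mann-Whitney:** use it only between arms, on change scores.
- **Cohen's d:** state which contrast it describes.
- **Choice of test:** delete the 2-SD rule and the data-driven switch between tests.
- **Club:** add it as a covariate only if athletes are randomised within clubs. If whole clubs are allocated, the club term cannot be estimated, and the report must say that the difference is confounded with club.

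The cost is analysis wording and one degree of freedom. Both VO2max measurements are already scheduled.

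### The rank test named for before-after comparisons in non-normal variables (Mann-Whitney U) is for independent samples, although the same athletes are measured twice; it is conservative and loses power as the pre-post correlation rises

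*Protocol article*

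**What the plan says.** Section 2.8 (Data Analysis) sets a two-branch rule. The parametric branch reads: "If the sample is normally distributed, Student’s t-test will be calculated to compare variables before and after the intervention". The rank branch opens with "If the sample is nonparametric" and continues: "the U-Mann Whitney test will be used to compare variables before and after the intervention". No paired rank test is named anywhere in the article.

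Section 2.4 (Outcomes) fixes the timing: "Measurements will be taken before and after the training period", with the pretest in week 5 and the post-test in week 12. Each athlete therefore supplies both values.

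The Introduction gives two objectives. The first is "to determine changes in the performance of high-level athletes after following an HRV-guided or a traditional training period", a within-arm question. The second is "to determine differences in the athletes’ performance after following both training protocols", a between-arm question. Section 2.8 does not tie either objective to a particular test.

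**The concern.** A before-after comparison in the same athletes is paired. The Mann-Whitney U test assumes two independent samples, so it judges the change against the spread between athletes rather than the spread of the individual changes. Athletes who start high tend to finish high. The stronger that tendency, the more irrelevant spread the test leaves in the error term.

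What is at stake is objective (i) for any variable judged non-normal. A real improvement within an arm could be reported as no significant change because the named test cannot use the pairing. This is not a detail left open by a condensed article: a specific test is named for a specific comparison, and the two do not match.

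**Working it through.** **Inputs from the protocol.** Section 2.5 gives n = 7 per group, SD = 1.5 mL/kg/min and d = 1.1. Sections 2.5 and 2.8 set significance at 0.05.

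**Assumptions.** Tests are two-sided, data are bivariate normal with equal SD at both times, and the pre-post correlation ρ is 0.5 to 0.9. The protocol gives no ρ and no expected within-arm change.

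**The plan's own figures.** The formula as printed gives 1.96² × 1.1²/1.5² = 2.07. With the ratio inverted, 1.96² × 1.5²/1.1² = 7.14, which matches the stated 7. The stated 93% power is reproduced (92.9%) by a two-group comparison with between-group variance 2 and within-group variance 1, which is a difference of 2 SD. With both variances at 2 the power is 68.1%. These are between-group figures. They enter here only as the source of n = 7 and of a 2 SD reference effect.

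**Why pairing matters.** For SD σ at each time, the mean change has variance 2σ²(1 − ρ)/n. An independent-samples analysis behaves as if it were 2σ²/n. Its standard error is therefore too large by 1/√(1 − ρ): 1.41, 1.83, 2.24 and 3.16 at ρ = 0.5, 0.7, 0.8 and 0.9. The same logic carries over to ranks.

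**Exact rejection regions at n = 7.**
- Mann-Whitney: U ≤ 8 or ≥ 41, size 3.8% if the samples were independent.
- Signed-rank: W ≤ 2 or ≥ 26, size 6/128 = 4.7%. Its smallest possible p is 2/128 = 0.016.

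**Two scales for the change.** The SD of the change scores is σ√(2(1 − ρ)), which is 1.00σ, 0.77σ, 0.63σ and 0.45σ at the four correlations. The scales coincide at ρ = 0.5, and the simulated powers agree there.

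**Simulated rejection rates, Mann-Whitney / signed-rank.**

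| True change | ρ = 0.5 | ρ = 0.7 | ρ = 0.8 | ρ = 0.9 |
|---|---|---|---|---|
| None (type I error) | 0.9% / 5% | 0.3% / 5% | 0.1% / 5% | 0.02% / 5% |
| 1 SD of change scores | 31% / 57% | 15% / 57% | 7% / 57% | 2% / 57% |
| 0.73 between-athlete SD | 15% / 34% | 13% / 53% | 12% / 69% | 11% / 93% |
| 1 between-athlete SD | 31% / 57% | 30% / 78% | 31% / 91% | 30% / 99% |
| 1.5 between-athlete SD | 70% / 88% | 73% / 98% | 75% / >99% | 75% / 100% |
| 2 between-athlete SD | 93% / 98% | 95% / >99% | 95% / 100% | 96% / 100% |

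The signed-rank entries in the first two rows are rounded to one value because they barely vary with ρ. The 0.73 row is 1.1/1.5 with 1.5 read as the between-athlete SD. Section 2.5 does not say whether 1.5 is an SD of values or of changes, nor that 1.1 is an expected change, so that row is illustrative.

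**How often the rank branch is reached.** Section 2.8 requires 95% of values to lie within two SD of the mean. One value outside fails the rule with 7 values (6/7 = 86%) and with 14 (13/14 = 93%). Simulated normal data fail in about 6% of sets of 7, in 10–12% if either time point may fail, and in about 42–43% if 14 values are pooled. The protocol does not say which set is checked.

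**The case against.** Several points on the other side stand.

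- **The test is only a fallback.** It applies to variables judged non-normal. The simulation uses normal data, most of which would go to the t-test at n = 7 unless the arms are pooled for the check. The figures therefore show the direction and rough size of the loss, not the performance on the variables that reach this branch.
- **Small n explains part of the loss.** At 0.73 between-athlete SD and ρ = 0.5 the signed-rank test itself has only 34% power.
- **The error is conservative.** With a positive correlation it does not inflate false positives.
- **The t-test sentence is not wrong.** A reader might infer that the parametric branch is unpaired too. The text does not say so, a paired t-test is the natural reading for before-after data, and an article may leave that word to the analysis plan. Only a clarification is warranted.

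The most charitable defence is that the sentence meant HRV-G against TRAD-G, where Mann-Whitney fits. The missing within-arm rank test would then be an omission from a condensed article rather than an error. But the sentence says before and after the intervention, so this reading departs from the text and does not remove the need to correct it.

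**Conclusion.** The point holds. As written, section 2.8 assigns an independent-samples rank test to paired values. The result is a test whose actual type I error is below 1% for ρ of 0.5 or more, and which gives up power that a paired test would keep. For a change of 1 SD of the change scores, power falls from about 57% to 31% at ρ = 0.5 and to 2% at ρ = 0.9. For a change of 1 between-athlete SD it stays near 31% whatever the correlation, while the signed-rank test rises from 57% to 99%.

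A reader might go further and conclude that real within-arm changes would usually be missed. The documents do not support that as a general statement, because they fix neither the expected change nor the correlation. Power is 70–75% at 1.5 between-athlete SD and 93–96% at 2. On the change-score scale, a 2 SD change is found 93%/76%/55%/22% of the time at ρ = 0.5/0.7/0.8/0.9.

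The consequence is confined to objective (i) and to variables routed to the rank branch. The comparison between arms is not affected.

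**What to change.** In section 2.8, name the exact Wilcoxon signed-rank test as the rank alternative for before-after comparisons within an arm. As a clarification, add that the t-test for the same comparison is paired. Keep the Mann-Whitney U test for HRV-G versus TRAD-G, for example on change scores.

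The cost is a few words. No extra athletes, measurements or data are needed, and the exact signed-rank test is usable with 7 pairs because it can reach p = 0.016.

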### 2.5. Sample Size and Power

Calculations to establish the sample size will be performed using RStudio 3.15.0 software (PBC, Boston, USA). The significance level will be set at *p* ≤ 0.05. According to the mean standard deviation established for VO_2max_ in a previous study [31] (SD = 1.5 mL/kg/min) and an estimated error (*d*) of 1.1, a valid sample size providing a 95% confidence interval (CI) in each group will be 7 (*n* = *CI*^2^ × *d*^2^/*SD*^2^). Thus, a final sample size of 7 for each group will provide a power of 93% if between and within a variance of 2.

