### 2.7. Allocation and Blinding

A block randomization method will be used to allocate participants to the groups, which will contain equal sample sizes. The block size will be determined by the data monitoring committee according to the statistical power provided. Blocks will be chosen randomly by tossing a coin to determine the participants’ assignment into the groups. This procedure will be carried out by the data monitoring committee. The athletes and the data monitoring committee will be blinded to the exercise group assignment.

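### Cohen's d with no small-sample correction named, at 7 athletes per arm, exaggerates non-zero standardised differences on average: about 7% between arms, about 7–15% within an arm depending on the standardiser

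*Protocol article*

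**What the plan says.** The protocol article names its effect-size measure twice in section 2.8 (Data Analysis): "The standardized mean differences (Cohen’s effect size) will be calculated together with the 95% confidence intervals" and, in the next sentence, "The effect sizes (ES) will be calculated using Cohen’s d [49". Neither sentence mentions a small-sample correction or says which SD is the denominator.

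Section 2.5 (Sample Size and Power) fixes "a final sample size of 7 for each group", and section 2.7 (Allocation and Blinding) plans equal groups. The objectives at the end of the Introduction cover both the change within each training group and the difference between groups, so d would naturally be used for both.

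Section 2.8 also plans means, SDs and ranges as descriptive data. It plans no mean difference in the original units with a confidence interval.

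**The concern.** Cohen's d divides a mean difference by an SD estimated from the same small sample. The reciprocal of that SD is on average larger than the reciprocal of the true SD, so d is on average further from zero than the quantity it estimates. The effect is negligible in large samples but not at 6 or 12 degrees of freedom.

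The standardised difference is the only effect estimate for which section 2.8 plans an interval, and the article stresses how few studies exist in elite endurance athletes. The reported values may therefore be used to plan later trials or enter a meta-analysis. Required sample size varies roughly as 1/d². A planner who took d at its expected value would get about 12% too few participants from the between-arm d (0.936² = 0.876). From a within-arm d with a 6-df standardiser the shortfall would be about 25% (0.869² = 0.754).

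**Working it through.** **Inputs from the protocol article.** 7 athletes per group (section 2.5), equal groups (section 2.7), Cohen's d (section 2.8).

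**The plan's own figures.** The article gives no figure for this bias. The figure used here is n = 7. It reproduces from the stated SD of 1.5 and error of 1.1 if the formula is read with the SD in the numerator: 1.96² × 1.5² / 1.1² = 7.14. The formula as printed gives 1.96² × 1.1² / 1.5² = 2.07. The stated 93% power reproduces (92.9%) in a two-group analysis of variance with a between-to-within variance ratio of 2. The printed formula and the variance wording are separate matters. This check needs only n = 7.

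**Bias formula.** For Normal data the mean and SD of a sample are independent, so

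E[d] / δ = 1 / J(v), with J(v) = Γ(v/2) / [√(v/2) · Γ((v − 1)/2)],

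where δ is the true standardised difference and v the degrees of freedom of the SD in the denominator.

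**Between arms.** v = 7 + 7 − 2 = 12.
J(12) = Γ(6) / [√6 · Γ(5.5)] = 120 / (2.449 × 52.34) = 0.936; 1/J = 1.068, an inflation of 6.8%.

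**Within an arm, baseline SD or SD of changes.** v = 7 − 1 = 6.
J(6) = Γ(3) / [√3 · Γ(2.5)] = 2 / (1.732 × 1.329) = 0.869; 1/J = 1.151, an inflation of 15.1%.

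**Cross-checks.** The usual approximation 1/(1 − 3/(4v − 1)) gives 6.8% and 15.0%. Simulation with 400,000 replicates gave 6.8–6.9% between arms. Within an arm it gave 15.2–15.5% on the SD of changes and 15.0–15.5% on the baseline SD.

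**Within an arm, averaged pre/post SD.** The inflation then depends on the pre-post correlation, which the article does not give. By simulation at assumed values:

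| Assumed correlation | Average inflation |
|---|---|
| 0 | about 7% |
| 0.5 | about 8% |
| 0.8 | about 11% |
| 0.95 | about 14% |

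At correlation 0 the two SDs together carry 12 df. As the correlation approaches 1 they carry little more than 6.

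**Scale against sampling error.** Take a true d of 0.73 for illustration; it is not a planned effect in the article.
- Between arms: bias 0.73 × 0.068 = 0.05, sampling SD about 0.61, ratio about 0.08.
- Within an arm, SD of changes: bias 0.73 × 0.151 = 0.11, sampling SD about 0.55, ratio about 0.20.

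**The case against.** The strongest reply is that section 2.8 names a standard descriptive measure, says nothing false about it, and leaves the correction and the denominator to a fuller document. The article never says that d will be uncorrected, and the source cited for it cannot be consulted here. This stands in part: the absence of a correction is inferred from the named estimator. But the article does choose an estimator, twice, and Hedges' g is a different named estimator that suits n = 7 better.

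The second reply is materiality. The bias is roughly a tenth to a fifth of a standard error. The t-tests, p-values and type I error do not involve it, and anyone who knows n and the denominator can correct a published d afterwards. All of that stands and limits the weight of the point. It is no reason to keep a bias that one multiplication removes.

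A reader might infer more than the article supports:

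- **That every reported effect will be too favourable to HRV-guided training.** The bias is away from zero. There is none if the true difference is zero, and if HRV-G is truly worse, d exaggerates the harm. It is also a bias in expectation, so a single estimate may fall well below the truth.
- **That 15% is the within-arm figure.** It holds only for a 6-df denominator, which the article does not specify.
- **That nothing in raw units is planned.** Means and SDs are. Only a raw-unit difference with an interval is absent.
- **That the planned confidence interval is wrong.** Its method is not stated. An exact noncentral-t interval would cover the true standardised difference without any J factor.

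**Conclusion.** The point holds as a minor improvement to the reported effect sizes. With 7 athletes per group, Cohen's d exaggerates the magnitude of a non-zero standardised difference on average by about 7% between arms. Within an arm the figure is about 15% with the baseline SD or SD of changes, or about 7–14% with an averaged pre/post SD over assumed correlations of 0 to 0.95.

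These figures rest on Normal data, athletes treated as independent, and all 7 per group analysed. They are not exact for variables that fall into the non-Normal branch of section 2.8. The trial's hypothesis tests do not change.

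**What to change.** In section 2.8:

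1. Replace Cohen's d with Hedges' g = d × J(df). At the planned size J is 0.936 between arms and 0.869 within an arm with a 6-df standardiser. Compute it from the numbers actually analysed.
2. Name the standardiser for the between-arm and the within-arm effect.
3. Report g with a 95% CI and state the interval method. The limits of an exact noncentral-t interval already refer to the true standardised difference and should not be multiplied by J.
4. For VO2max, also report the mean difference in mL/kg/min with its 95% CI. This is a companion reporting improvement; the bias in d does not itself require it.

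The cost is a sentence or two of text, with no extra data, athletes or procedures. The downside is that the reported effect sizes become slightly smaller.

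### Pearson r is fixed for all relationships, even for variables the plan itself classes as nonparametric and for the ordinal RPE rating, so with 7 to 14 athletes one extreme athlete can create a significant correlation

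*Protocol article*

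**What the plan says.** All the analysis text is in section 2.8, Data Analysis.

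- **Normality check.** A Shapiro-Wilk test is planned, together with a working rule that "95% of values will have to be within two standard deviations of the mean".
- **What follows from it.** Normal variables go to Student's t-test. For the others, "If the sample is nonparametric, the U-Mann Whitney test will be used to compare variables before and after the intervention". This branch is tied to the before/after comparison and to nothing else.
- **Correlations.** "The relationship between variables will be assessed using the Pearson r correlation coefficient". There is no condition on distribution and no rank alternative.
- **Interpretation.** "If r is higher than 0.7, the determination coefficient (r^2^) will be used to determine the percentage of Y variation". The general criterion is "Significance will be accepted at *p* ≤ 0.05".

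Two other places bear on the point. Section 2.5 plans 7 athletes per group, 14 in all. Section 2.4 lists RPE among the secondary outcomes, and the description of the 3000 m test defines it on the modified CR-10 scale from 0 to 10.

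**The concern.** The plan applies its normality logic to one task and drops it for the next. Section 2.3 shows that the authors link parametric methods to normality, since HRV is log-transformed for that reason. Yet in section 2.8 a variable that has failed the plan's own check is still correlated by Pearson r, and an r above 0.7 is then read as a share of variation explained. RPE is an ordinal rating, for which a rank coefficient is the natural choice whatever its histogram looks like.

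The practical risk lies in the sample size. With 7 or 14 points, one athlete far from the rest on both variables carries much of the cross-product sum. A relationship could then be reported that reflects one person. Naming a coefficient without condition is a choice the article makes, so this is not a detail left to a fuller plan.

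**Working it through.** **Inputs from the article:** n = 7 per group and 14 in total (2.5); significance at p ≤ 0.05, taken as two-sided; trigger r > 0.7 for r²; the two-SD rule (2.8).

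**Assumptions, not in the article:** two unrelated Normal variables, with one athlete placed at k SD on both. The value of k is illustrative. The article states no figure for correlations, so there is none to reproduce.

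**Step 1. Critical r.** r_crit = t/√(n − 2 + t²), with t the 97.5% point on n − 2 degrees of freedom.
- n = 14: 2.179/√(12 + 4.748) = 0.532
- n = 7: 2.571/√(5 + 6.608) = 0.754

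**Step 2. What one athlete contributes.** With c = k²(n − 1)/n, the outlier adds about c to the cross-product and to each sum of squares, and the other athletes add about n − 2 to each sum of squares. So r is roughly c/(n − 2 + c).
- n = 14, k = 3: c = 9 × 13/14 = 8.36; r ≈ 8.36/20.36 = 0.41 (simulated median 0.43)
- n = 14, k = 4: c = 16 × 13/14 = 14.86; r ≈ 14.86/26.86 = 0.55 (0.57)
- n = 7, k = 3: c = 9 × 6/7 = 7.71; r ≈ 7.71/12.71 = 0.61 (0.65)
- n = 7, k = 4: c = 16 × 6/7 = 13.71; r ≈ 13.71/18.71 = 0.73 (0.76)

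At k = 4 the simulated median lies just above the critical value for both sample sizes.

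**Step 3. Simulation, 200,000 runs per row.**

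| n | k | Pearson p ≤ 0.05 | Spearman p ≤ 0.05 | Pearson r > 0.7 | Spearman > 0.7 | Variable flagged by two-SD rule |
|---|---|---|---|---|---|---|
| 14 | none | 5% | 5% | 0.3% | 0.3% | 42% |
| 14 | 3 | 29% | 8% | 6% | 1.3% | 84% |
| 14 | 4 | 61% | 8% | 18% | 1.3% | 99.5% |
| 7 | none | 5% | 5% | 4% | 4% | 6% |
| 7 | 3 | 29% | 9% | 40% | 15% | 19% |
| 7 | 4 | 53% | 9% | 67% | 15% | 44% |

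**Step 4. The two-SD rule.** One value beyond two SD leaves 13/14 = 92.9% or 6/7 = 85.7% inside, so a single such value classes the variable as non-normal. At n = 7 the largest possible standardised deviation is 6/√7 = 2.27, because an outlier inflates the SD against which it is judged. That is why the rule misses many outliers there. The Shapiro-Wilk test was not simulated.

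**Step 5. Skewness without an outlier.** For independent lognormal variables (8,000 runs) Pearson's error rate is 5.3% to 6.3%.

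**Step 6. Arm mixing, only if all 14 athletes are pooled.** If both of two outcomes that are unrelated within arm shift by d SD between arms, the pooled population r is (d²/4)/(1 + d²/4).

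| d | Pooled population r | p ≤ 0.05 | r > 0.7 |
|---|---|---|---|
| 0.73 (1.1/1.5 from 2.5, read as a difference) | 0.12 | 7% | 0.8% |
| 1 | 0.20 | 11% | 1.6% |
| 2 | 0.50 | 53% | 17% |
| 3.06 | 0.70 | 94% | 64% |

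Adjusted for arm, the rates are about 5% and 0.4% in every row.

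**The case against.** **The outlier is hypothetical.** Nothing in the article suggests that an athlete will lie 3 to 4 SD out on two unrelated variables at once. RPE is bounded at 0 to 10, and ordinary skewness, the usual worry for lactate, barely moves Pearson's error rate. This stands. The percentages describe vulnerability, not expected frequency, and the case for a rank coefficient for RPE rests on its ordinal scale.

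**The two-SD rule is a poor switch.** It classes 42% of truly Normal variables as non-normal at n = 14, so tying Spearman to it will often change the coefficient needlessly. This also stands, but the price is only a slight loss of efficiency. Giving both coefficients for the remaining variables makes the result depend less on the switch.

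**Spearman is not a full cure at n = 7.** It still exceeds 0.7 in 15% of runs with the outlier. That is true, though Pearson does so in 40% to 67%.

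**A stronger reading concerns the arms.** A reader might infer that the difference between arms will itself produce correlations that are reported as explained variation, since the Discussion expects the HRV-guided group to do better. The article does not support this. It never says that arms, or weeks 5 and 12, are pooled, and a fuller plan may settle that. The 2 SD shift behind the 53% is inferred from an ambiguous sentence, "Thus, a final sample size of 7 for each group will provide a power of 93% if between and within a variance of 2": a between-to-within ratio of 2 gives 92.9% power, but both variances equal to 2 gives 68%. The sentence concerns VO2max alone. Even at 2 SD in both outcomes, r passes the plan's 0.7 trigger in only 17% of runs.

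**Conclusion.** The point holds as an inconsistency in stated methods: the normality branch in section 2.8 is not carried over to correlations, and Pearson r is prescribed without condition, including for an ordinal rating.

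Under the illustrative assumption of one athlete 3 to 4 SD out on two unrelated variables, false significance rises from 5% to between 29% and 61% at n = 14 and between 29% and 53% at n = 7, where Spearman stays near 8% to 9%. At n = 14 and 4 SD the plan's own rule detects the outlier almost always and then does nothing with it for correlations. At n = 7 it misses the outlier more often than not.

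Arm mixing warrants a precaution and is not a demonstrated fault. The overall weight is small: neither objective in the Introduction and no outcome in section 2.4 depends on a correlation, so the primary conclusion is unaffected.

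**What to change.** In section 2.8, after the Pearson sentence, state that:

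1. Spearman's coefficient is used for RPE and for any variable classed as nonparametric by the plan's checks.
2. For the other variables Spearman is reported beside Pearson, because the two-SD rule misses many outliers at n = 7.
3. Every coefficient is given with its 95% confidence interval.
4. If athletes from both arms are analysed together, the correlation is computed within arm or adjusted for arm.

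This is a change of one or two sentences and needs no further data. It costs a slight loss of efficiency when the data are truly Normal, and one degree of freedom where arm is adjusted for (11 instead of 12 with 14 athletes).
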